### Outcome measures

The primary outcome measure of the DIABAR-trial is glycemic control, as measured by the difference in Hba1c 12 months after RYGB and OAGB. Glycemic control at 6 months, 2–5 and 10 years of follow-up, and the remission of T2DM at 1–5 and 10 years of follow-up are secondary outcome measures. For remission of diabetes, we will use the proposed definition according to ADA consensus report 2021 primarily (Hba1c < 6.5%), and in a secondary analysis, the more strict cut-off < 5.7% will be used [19]. Other secondary outcome measures are related to the interplay of obesity, NAFLD/NASH, and cardio-vascular performance. Table 1 shows the schedule of enrolment and study procedures (SPIRIT-format). All measurements will be performed by the researchers and physicians according to a standard operating procedure.

*Demographics* consist of age, sex, ethnic background, medical history, use of medication, history of weight-change, intoxications, educational level, employment status, and physical activity. Prior to surgery, patients will be asked about their expectations of metabolic surgery in terms of weight loss.

*Biometric data* consist of weight, height, waist to hip ratio, temperature, bioelectrical impedance (BIA), electrocardiogram (ECG), blood pressure, pulse, stroke volume, cardiac output, and systemic vascular resistance (Nexfin).

*Dutch versions of validated questionnaires* are used for evaluation of psychological measures. This includes quality of life, self-efficacy, hunger and craving, social support, depression, and body image, as previously described in the protocol of the BARIA-study [15]. Food intake is registered using food diaries. Gastro-intestinal complaints are assessed with the gastro-intestinal quality of life (GIQLI) questionnaire [20].

*Peripheral blood* will be drawn at various time points as part of the regular follow-up and includes hemoglobin, leukocytes, C-reactive protein, HbA1c, glucose, c-peptide (only baseline), electrolytes, kidney function, hepatic enzymes, lipid profile, iron, vitamins, and thyroid profile.

*Mixed meal test*, a 2-h oral mixed meal test (MMT), will be performed three times in the course of the study [21]. During the MMT, the patient will consume two 125 ml Nutridrink compact drinks (Nutricia®). At set time points during this test, blood will be obtained through an intravenous line and will be used to measure insulin sensitivity, plasma metabolites, and bile acids.

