### Statistical analysis

#### Power calculation and sample size

Sample size calculation was performed based on a retrospective analysis of patients after RYGB (*n* = 90) and OAGB (*n* = 37). Patients were matched in a 3:1 ratio on baseline age, BMI, and gender. The mean pre-operative Hba1c in the RYGB group was 7.5 ± 1.4% and 7.5 ± 1.5% in the OAGB group (*p* = 0.97). Null hypothesis is as follows: there is no difference in decrease of Hba1c at 12 months after RYGB or OAGB in patients with T2DM. Alternative hypothesis: the decrease in Hba1c after OAGB is higher than after RYGB in patients with T2DM at 12 months after surgery. For sample size calculation, the mean Hba1c of both groups was compared with a two-sided significance level of *P* < 0.05 and a power of 80%. Based on the retrospective results, 100 subjects per group will be required. Considering a 10% dropout rate, 220 patients are needed.

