#### Analysis of endpoints

The statistical analyses will be performed using SPSS statistical software (IBM corporation, New York, USA). Data will be expressed as mean, standard deviation, or median and range, as appropriate. Differences in categorical variables will be evaluated with the chi-square or the Fisher exact test, as appropriate; continuous data will be compared with the Student *t* test or Mann-Whitney *U*. Multivariate analysis and ANOVA for repeated measures will be used. *P*-values < 0.05 will be considered statistically significant. Clinical complications will be evaluated by an independent adjudication committee. An interim analysis will be performed at 60 patients per group. A modified intention to treat analysis will be performed (all randomized patients that initiate treatment in the arm they are allocated to, i.e., exempting those who do not undergo surgery at all) in which “last value carried forward” will be used for missing observations. A per-protocol analysis will be carried out as well to account for effects of revisional surgery (i.e., revision from OAGB to RYGB). For this analysis, only data of patients gathered before revisional surgery will be used.

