## Discussion

The STAMPEDE-trial has shown that surgery is more effective than medical treatment in patients with obesity and T2DM [2]. Still, it has not been established which metabolic surgery is the most powerful in the treatment of T2DM. In the Netherlands, the RYGB is the most performed bariatric and metabolic procedure [23]. With a peri-operative mortality rate between 0.1 and 0.41%, a rate of serious adverse events within the first 30 days after surgery ranging from 1.38 to 8.3%, and sustainable weight loss at follow-up, the RYGB can be considered a safe treatment for severe obesity [24–30]. The remission of T2DM after RYGB is reported to be between 50 and 80% depending on length of follow-up [4, 5, 31–33]. Although the RYGB has good results, it is considered an advanced and complex laparoscopic procedure, with a learning curve between 50 and 100 cases [34]. The OAGB was introduced as a simplified version of the RYGB and from start the OAGB has reported promising results in terms of weight loss, post-operative morbidity and mortality [35–43]. In single-arms studies, the short-term remission of T2DM is reported to be between 84 and 92% [42, 43]. The DIABAR-trial will demonstrate which of these two procedures is the most beneficial in patients suffering from T2DM and severe obesity. This information will aid the patient and physician in selecting the most potent surgical treatment. By extension, it is important to weigh the metabolic advantages of these procedures against the concerns in the post-operative course. Besides the more obvious surgical complications, such as post-operative bleeding and anastomotic leakage, seen after both RYGB and OAGB, there are some procedure-specific concerns. Internal herniation (IH) is a potentially serious complication after RYGB as it harbors the risk of small bowel obstruction and subsequent small bowel ischemia; after OAGB, IH is seldomly seen [44–47]. The OAGB has been surrounded by controversy for its potential to cause biliary reflux and to induce subsequent metaplasia, dysplasia, and carcinoma of the gastric remnant and/or the esophagus [48, 49].

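### Unrestricted last value carried forward can put pre-operative HbA1c into the 12-month primary endpoint and early values into outcomes up to 10 years

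*Protocol article*

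**What the plan says.** The section Analysis of endpoints defines a modified intention-to-treat analysis of operated patients, "exempting those who do not undergo surgery at all", "in which “last value carried forward” will be used for missing observations". No other method for missing data is named. The per-protocol analysis in the same section deals with revisional surgery.

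The primary outcome is glycemic control, "as measured by the difference in Hba1c 12 months after RYGB and OAGB" (Outcome measures). The null hypothesis is put in terms of change: "there is no difference in decrease of Hba1c at 12 months after RYGB or OAGB in patients with T2DM" (Power calculation and sample size). Secondary outcomes include "Glycemic control at 6 months, 2–5 and 10 years of follow-up" and remission at 1–5 and 10 years.

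HbA1c is part of the regular laboratory work (Outcome measures). Table 1 marks that work at screening, day of surgery, 6 months, 1 year, 2 years, and 3, 4, 5 and 10 years. Nothing is marked at 14 or 42 days.

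The sample size is 100 per group, then: "Considering a 10% dropout rate, 220 patients are needed".

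**The concern.** Carrying a value forward assumes that nothing has changed since it was measured. Here the last value may predate the operation whose effect is being measured, in a trial whose own Background says that surgery brings about rapid remission.

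Three things are at stake:

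- **Primary endpoint.** Similar loss in both arms, with pre-operative values carried, shrinks the difference and adds variance. Unequal loss creates a difference where none exists. The rule is therefore not reliably conservative.
- **Long-term outcomes.** A patient in remission at an early visit who is then lost stays in remission up to year 10. Relapse, which long follow-up should reveal, would be hidden.
- **Precision.** Filled values count as observed, so standard errors do not reflect the missing information.

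The 10% inflation does not cover this. It makes up for patients who leave the analysis, whereas this rule keeps them in with values from another time.

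**Working it through.** **1. What is carried, by pattern of missing visits (from Table 1)**

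| Operated patient misses | Value used at 12 months |
|---|---|
| 12 months only | 6-month HbA1c |
| 6 and 12 months | pre-operative HbA1c, decrease = 0 |

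The first pattern is much less harmful than the second.

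**2. The plan's own figure.** 200 × 1.10 = 220, as stated (200 / 0.90 would be 223, a trivial difference). The 100 per group cannot be reproduced, because the assumed 12-month difference and SD are not given. Inverting the usual formula at two-sided 5% and 80% power:

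standardized difference = (1.960 + 0.842) × √(2/100) = 0.396.

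This is 0.396 HbA1c points if the 12-month SD is 1.0, and 0.574 if it is 1.45.

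**3. Inputs**

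- From the article: pre-operative mean 7.5 in both arms, SD 1.4 and 1.5 (1.45 used here); 220 patients at 1:1, so 110 per arm; 10% dropout.
- Assumed: 12-month RYGB mean 6.0–6.5 (a fall of 1.0–1.5 points); 12-month SD 1.0–1.45; true difference as in step 2; a two-sample comparison of 12-month HbA1c by normal approximation; data missing at random.

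**4. Power with equal loss.** If a share m of an arm carries pre-operative values:

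- arm mean = (1 − m) × μ₁₂ + m × 7.5
- arm variance = (1 − m) × SD₁₂² + m × 1.45² + m(1 − m) × (7.5 − μ₁₂)²
- power = Φ(difference / SE − 1.960)

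The estimated difference is (1 − m) times the true one. Worked case with m = 10%, RYGB mean 6.0, SD 1.0:

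- RYGB: mean 0.9 × 6.0 + 0.1 × 7.5 = 6.15; variance 0.9 + 0.210 + 0.09 × 1.5² = 1.313
- OAGB (12-month mean 6.0 − 0.396 = 5.604): mean 5.793; variance 0.9 + 0.210 + 0.09 × 1.896² = 1.434
- difference 0.357; SE = √((1.313 + 1.434)/110) = 0.158; power = Φ(2.257 − 1.960) = 62%

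Observed data only, 99 per arm: 0.396 / √(2/99) = 2.788, power 79.6%.

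All carried values from 6 months, distributed like the 12-month values and showing the full difference: 0.396 / √(2/110) = 2.938, power 83.6%. This is nominal, because filled values count as real.

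Over the assumed means and SDs, with 10% missing per arm:

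| Carried values | Estimate / truth | Power |
|---|---|---|
| all pre-operative | 90% | 62–72% |
| half pre-operative, half 6-month | 95% | 72–78% |
| one fifth pre-operative, rest 6-month | 98% | 79–82% |
| all 6-month, full difference | 100% | 84% (nominal) |
| observed data only, nothing carried | 100% | 80% |

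**5. Type I error with unequal loss.** With no true difference and pre-operative values carried, the spurious difference is (m₂ − m₁) × fall. Worked case with 5% versus 15%, fall 1.5, SD 1.0: difference 0.10 × 1.5 = 0.15; variances 1.162 and 1.452; SE = √(2.614/110) = 0.154; ratio 0.973; two-sided rejection about 16%.

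| Missing | Carried values | Spurious difference | Type I error |
|---|---|---|---|
| 5% vs 15% | all pre-operative | 0.10–0.15 | 8–16% |
| 5% vs 15% | half pre-operative, rest 6-month | 0.05–0.075 | 6–8% |
| 8% vs 12% | all pre-operative | 0.04–0.06 | 5.5–7% |

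**The case against.** The strongest reply is that the harm is conditional. A pre-operative value reaches the primary endpoint only if an operated patient misses both the 6- and the 12-month sample. If most missing patients have a 6-month value, little or no nominal power is lost. Patients never operated on are excluded, so part of the 10% allowance may never be imputed. Nothing in the article suggests that loss will differ threefold between two surgical arms with the same scheduled visits. All of this stands, and it limits what can be said about size. It does not defend the rule, which has no safeguard against the harmful pattern and still treats filled values as observed. Nor would an unseen analysis plan make the stated rule sound.

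Three stronger readings are tempting but not supported:

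- **That the rule certainly biases the comparison and costs power.** The tables above show that this depends on which values are carried and on imbalance between arms.
- **That its effect on 10-year remission can be calculated from the article.** The Discussion says "The remission of T2DM after RYGB is reported to be between 50 and 80% depending on length of follow-up". That is a range across reports, not one cohort declining from 80% to 50%. Later visits would also supply more recent values for many patients who are lost.
- **That filled values necessarily enter the repeated-measures ANOVA.** The article says "Multivariate analysis and ANOVA for repeated measures will be used" but does not say for which endpoint, nor link it to the carried values.

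**Conclusion.** The point holds as a defect in a stated rule. As written, last value carried forward lets a pre-operative HbA1c count as a 12-month result and lets early post-operative values count as results up to 10 years, with no restriction and no alternative method named.

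The consequence for the primary comparison ranges from negligible to serious: power between about 62% and a nominal 84%, and type I error from close to 5% up to about 16%. The harsh ends need every carried value to be pre-operative; the 16% also needs 5% versus 15% loss, a 1.5-point fall and a 12-month SD of 1.0. The 12-month means and SD, the 6-month values and the pattern of missing data are assumptions. For the long-term outcomes, the concealment of relapse follows from the rule itself, but its size cannot be derived from the article.

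**What to change.** Do not use last value carried forward as the primary handling of missing data. Instead:

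- estimate the 12-month HbA1c contrast from a likelihood-based mixed model on all observed HbA1c values including baseline, or by multiple imputation;
- use multiple imputation for remission;
- keep last value carried forward, if at all, as a labelled sensitivity analysis.

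Model terms and details can go in the analysis plan. The defect does not require the repeated-measures ANOVA to be replaced throughout, nor one particular form of sensitivity analysis.

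The cost is a change of wording and slightly more analysis work, with no new data. The price is reliance on a missing-at-random assumption, which a sensitivity analysis can examine. Trial status describes recruitment as ongoing when the article was written. The change should be fixed in writing before outcomes are compared by arm.

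### The per-protocol cut-off is tied to a revision that can occur only in the OAGB arm, which can bias that comparison in a direction the plan does not let one determine

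*Protocol article*

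**What the plan says.** Protocol article, Analysis of endpoints, plans two analyses.

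- **Modified intention-to-treat:** "A modified intention to treat analysis will be performed (all randomized patients that initiate treatment in the arm they are allocated to"; patients never operated on are left out. The last value carried forward "will be used for missing observations". No cut at revision is stated.
- **Per-protocol:** "A per-protocol analysis will be carried out as well to account for effects of revisional surgery (i.e., revision from OAGB to RYGB"). The rule then follows: "For this analysis, only data of patients gathered before revisional surgery will be used".

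Under Outcome measures, the primary outcome is "glycemic control, as measured by the difference in Hba1c 12 months after RYGB and OAGB". The secondary outcomes include "Glycemic control at 6 months, 2–5 and 10 years of follow-up", with diabetes remission also followed to 10 years. Table 1 schedules the GIQLI questionnaire and the surgical endpoints over the same period.

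The Discussion names a specific worry for each operation. For RYGB it is internal herniation. For OAGB it says: "The OAGB has been surrounded by controversy for its potential to cause biliary reflux".

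**The concern.** The trigger for the cut is defined as conversion of an OAGB into an RYGB. A patient allocated to and operated with RYGB cannot have that event. A revision after RYGB therefore leaves the patient's later data in, while a revision after OAGB takes them out. The two arms are then compared under different rules, and the difference depends on something that happens after randomization.

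At stake is the long-term per-protocol comparison. Revisions accumulate, so the share of OAGB patients whose data are cut cannot fall from one visit to the next. By years 5 and 10 the analysis sets RYGB patients, whatever happened to them, against OAGB patients whose data stop at revision. HbA1c, remission, GIQLI and late complications are all followed that far.

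**Working it through.** **1. Does the text tie the cut to one arm?**
- The trigger is introduced with *i.e.*, which defines. The same section uses *i.e.* to define who is exempt from the modified intention-to-treat set. The Exclusion criteria use *e.g.* when they give examples.
- The next sentence, that "only data of patients gathered before revisional surgery will be used", names no arm, but it reuses the term just defined.
- Nothing elsewhere in the article extends the rule to a revision after RYGB.

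The literal reading is a cut in the OAGB arm only.

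**2. A yardstick.** The article gives no figure for revision or for the per-protocol analysis, so there is none to reproduce. Its 100 per group cannot be rebuilt either, because no 12-month difference or postoperative SD is stated. The difference that 100 per arm can detect is used here only as a scale (two-sided 5%, power 80%, preoperative SDs of 1.4 and 1.5):

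difference = SD × √(2/100) × (1.960 + 0.842) = 0.396 × SD

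- SD 1.4: 0.55 points
- SD 1.5: 0.59 points

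**3. Shift in the OAGB mean if later values are left missing.** Let r be the share of OAGB patients revised by a visit. Let g be HbA1c in revised minus unrevised patients at that visit. Both are assumptions. If unrevised patients have mean m, the full arm has m + r × g and the cut arm has m. The shift is therefore −r × g, and a negative shift favours OAGB.

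The last column is the simulated chance of a significant result in favour of OAGB when the arms truly do not differ. The nominal value is 2.5%. The simulation used 100 per arm, SD 1.45, a t test, 20,000 runs, and revised patients dropped from OAGB only.

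| r | g (points) | Shift (points) | False result for OAGB |
|---|---|---|---|
| 2% | +1.0 | −0.02 | 3.1% |
| 5% | +1.0 | −0.05 | 4.5% |
| 10% | +1.0 | −0.10 | 6.9% |
| 10% | 0 | 0 | 2.4% |
| 10% | −0.5 | +0.05 | 1.5% |

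At g = +1, the shift reaches a tenth of the detectable difference when r is 0.055/1 = 5.5% (SD 1.4) to 0.059/1 = 5.9% (SD 1.5).

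**4. If values are carried forward after the cut.** The article states this only for the modified intention-to-treat analysis. If it also applied here, the shift would be r × (last value before revision − value actually seen at the visit). A poor value before revision would then stay in the OAGB arm. The sign is again open, and values would still be frozen in one arm only.

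**5. A reflux outcome.** Assume 10 of 100 OAGB patients have severe reflux and 5 of them are revised. After the cut, later prevalence is 5/95 = 5.3%. Without the cut it lies between 5/100 = 5.0% (revision relieves all five) and 10/100 = 10% (it relieves none). The cut can therefore raise the figure slightly or nearly halve it.

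**6. The same rule in both arms.** With shares rO and rR and a common g, the net shift is −(rO − rR) × g. At g = +1:
- rO = 10%, rR = 5%: −0.05, against −0.10 under the one-arm rule.
- rO = rR = 5%: 0, against −0.05 under the one-arm rule.

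**The case against.** **The rule may have a sound purpose.** Conversion to RYGB moves the patient to the comparator operation. Stopping there avoids crediting OAGB with results obtained after an RYGB, and the sentence that does the cutting names no arm. That purpose is legitimate, and both arms may have been meant. It does not explain why a revision after RYGB should go unmentioned, and if both arms were meant the definition still needs correcting.

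**The analysis is additional.** The modified intention-to-treat analysis has no stated cut at revision and also covers the long-term outcomes. Late complications and readmissions are already surgical endpoints, and complications are adjudicated independently. This stands and limits the weight of the point. Revision itself, however, is not listed among the surgical endpoints.

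**A reader might infer that the rule removes failures and flatters OAGB, increasingly so with time.** The documents do not support this.
- They give no reason for revision. The Discussion mentions a potential for biliary reflux, which is not a glycemic failure.
- The sign of g is unknown, and a growing bias towards OAGB would need g above zero.
- Patients are censored at revision, not excluded, so their earlier HbA1c, GIQLI scores and complications remain.
- For reflux, the direction depends on whether revision relieves it.

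**Patients given the operation they were not allocated to.** Their place in the per-protocol set may be settled in the full protocol, so nothing is made of it here.

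**Conclusion.** The point holds as a defect in the definition. As written, follow-up in the per-protocol analysis can be cut at revision in the OAGB arm only. That can bias the comparison, and the share of OAGB patients exposed can only grow over the 10 years. The direction cannot be determined from the article.

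Over the assumed range (2% to 10% revised, HbA1c from 0.5 points lower to 1 point higher in revised patients), the shift runs from −0.10 to +0.05 points. That is small beside a detectable difference of 0.55 to 0.59. These sizes assume that values after the cut are left missing. The 12-month primary comparison is little affected, on the assumption that few revisions occur within the first year. This is a minor point, worth correcting because the correction costs almost nothing.

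**What to change.** Amend the per-protocol text as follows:

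1. Define revisional surgery identically for both arms, as any revisional bariatric procedure after RYGB or OAGB.
2. Apply the same cut-off in both arms, and state how values after it are handled (left missing or carried forward), again alike in both.
3. Use the same analysis model as for the primary comparison.
4. Interpret the result as supportive of the modified intention-to-treat analysis. A common rule removes the asymmetry by design, but if revision rates or the patients revised differ between arms, some bias can remain.
5. Report revision itself as an event in the between-arm comparison of complications, so that what the cut removes is visible.

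The cost is a few sentences in the protocol and analysis plan. Slightly more RYGB data are cut from the per-protocol analysis, and no new data are needed. The article describes recruitment as ongoing, so the change is best made before outcomes are compared by arm.

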### Ethics and permissions

The study will be conducted in accordance with the Declaration of Helsinki and “good clinical practice.” Ethical approval has initially been granted by the Institutional Review Board of Slotervaartziekenhuis en Reade, Amsterdam, the Netherlands. In 2019, the study was transferred to and approved by the Institutional Review board of Amsterdam UMC, location AMC, Amsterdam, the Netherlands (registered under NL61882.048.17). A data monitoring committee has not been installed. Auditing will be performed (at least) annually, independent from investigators and the sponsor.

